**Results:**

Participants are currently being recruited. The first participant was enrolled in June 2023, which marked the official start of the experiment. As of the submission of the paper, there were 23 participants. The recruitment process is expected to continue until June 2025, at which point the processing and analysis of data will begin. As of May 15, 2024, up to 30 people have been enrolled in this clinical trial.

**Conclusions:**

This study will provide data on the effects of Tongdu Xingshen acupuncture on cerebral iron deposition as well as somatic iron metabolism in patients with VCI. These results will help to prove whether Tongdu Xingshen acupuncture can improve VCI by regulating brain iron deposition and body iron metabolism, which will provide the clinical and theoretical basis for the wide application of acupuncture therapy in VCI rehabilitation.

**Trial Registration:**

China Clinical Registration Agency ChiCTR2300072188; https://tinyurl.com/5fcydtkv

**International Registered Report Identifier (IRRID):**

PRR1-10.2196/56484

## Introduction

Vascular cognitive impairment (VCI) is a series of clinical syndromes that encompasses mild cognitive impairment to severe vascular dementia (VD) caused by cerebrovascular disease and its risk factors [1]. VCI accounts for 15% to 20% of all patients with dementia in North America and Europe, and up to 30% of patients with dementia in Asia, making it the second most prevalent type of dementia after Alzheimer disease [2]. The persistent and progressive decline of higher brain functions, such as learning, memory, and executive functions, caused by VCI is a difficult problem in clinical rehabilitation, which seriously affects patients’ quality of life and involves a severe burden for families and society. Although donepezil and memantine may slow the progression of VCI, there are currently no effective clinical drug options for VCI from a clinical perspective [3,4]. Although nonpharmacological treatments such as aerobic exercise and cognitive rehabilitation training, as well as early control of risk factors such as blood pressure, lipids, and blood glucose, have been reported to have positive effects on the prevention and treatment of VCI, a range of issues limit the effective treatment of VCI, including a lack of clinical research, low compliance, lengthy interventions, and variable efficacy [5-8]. Therefore, it is important to find safe, effective, and widely applicable treatment methods for the clinical treatment and development of VCI.

Numerous studies have indicated that traditional Chinese medicine (TCM) can play an important role in the treatment of VCI [9,10]. In particular, acupuncture has the unique advantages of simplicity, convenience, safety, and effectiveness in the treatment of VCI [11]. According to the understanding of VCI in Chinese medicine, in which the “brain” and “governor vessel” play key roles in regulating the “vital spirit” and brain function, the “deficiency of the medulla oblongata and loss of the use of the spiritual mechanism” is considered to be the fundamental pathogenesis of VCI, leading to the development of the Tongdu Xingshen treatment principle. Several prior clinical studies in our laboratory and meta-analyses published by other researchers have demonstrated that acupuncture is effective in improving cognitive function and enhancing overall outcomes in patients with a history of stroke [12-14]. However, the in-depth mechanisms of Tongdu Xingshen acupuncture treatment for VCI require further validation and exploration.

The pathogenesis of VCI is complex. Previous studies of the pathogenesis of VCI have mainly focused on blood-brain barrier disruption, secondary inflammation, excitatory amino acid toxicity, cell autophagy, and apoptosis [15,16]. With the discovery of ferroptosis and the in-depth study of its mechanism of occurrence, more and more scholars believe that it plays an important role in central nervous system diseases [17,18]. By exploring the relationship between serum iron metabolism, brain iron deposition, and cognitive impairment, researchers in various countries, including China, have found that iron deposition can lead to the development of inflammation, abnormal protein aggregation, and degeneration in the central nervous system, which in turn causes a progressive decline in cognitive function [19,20].

Quantitative susceptibility mapping (QSM) is a postprocessing technique developed in recent years on the basis of sensitivity-weighted imaging (SWI), which enables to quantify the magnetic susceptibility properties of tissues in vivo [21,22]. The ability to measure brain iron content, which is quantified by the magnetization rate values obtained from QSM calculations, raises the possibility of investigating ferroptosis in VCI.

Therefore, the proposed study will examine brain iron deposition and body iron metabolism as entry points and use a clinical randomized controlled study design to investigate the clinical efficacy and possible mechanism of action of Tongdu Xingshen acupuncture to treat VCI with a view to providing a scientific basis for the clinical application of acupuncture.

## Methods

### Research Objectives

The primary objectives of this randomized controlled trial will be twofold: (1) to observe the clinical efficacy of Tongdu Xingshen acupuncture in patients with VCI and provide feasible and affordable acupuncture treatment for patients with VCI and (2) to investigate whether Tongdu Xingshen acupuncture improves the clinical performance of patients with VCI by affecting brain iron deposition and body iron metabolism and reveal the potential central and peripheral mechanisms of acupuncture in the treatment of vascular cognitive disorder.

### Trial Design and Setting

The proposed protocol involves a randomized controlled clinical trial to investigate whether Tongdu Xingshen acupuncture can improve the clinical performance of patients with VCI by regulating brain iron deposition and body iron metabolism. In total, 42 patients with VCI hospitalized at the First Affiliated Hospital of Henan University of Traditional Chinese Medicine from May 2023 to December 2025 and 21 healthy participants will be included in the study. Participants will be divided into acupuncture, conventional treatment, and healthy control groups according to a ratio of 1:1:1, with 21 participants in each group. The control group (n=21) will receive conventional medical and cognitive rehabilitation treatment, the acupuncture group (n=21) will receive professional acupuncture treatment by a professional acupuncturist on the basis of the conventional treatment, and the healthy control group (n=21) will not receive any intervention. All of the above treatments will be performed for 4 weeks, 6 times per week. Brain iron deposition and serum iron metabolism will be measured at week 0 (baseline) and week 4 of treatment using SWI and blood biochemistry. In parallel, a neuropsychological test battery including the Mini-Mental State Examination (MMSE), Montreal Cognitive Assessment (MoCA), and Clinical Dementia Rating will be administered to evaluate comprehensive cognitive function and clinical symptoms. Details of the proposed study process are presented in Figure 1 and Table 1.

**Figure 1 figure1:**
[figure not shown]
Flowchart of the trial. CDR: Clinical Dementia Rating; MMSE: Mini-Mental State Examination; MoCA: Montreal Cognitive Assessment; SWI: sensitivity-weighted imaging; VCI: vascular cognitive impairment.

**Table 1 table1:** Timing of treatment assessments and data collection.

Time point			Enrollment (week –1)		Baseline assessment (week 0)		Treatment phase (weeks 1-4)		Assessment of efficacy (week 5)
Sign informed consent			✓						
Demographic information			✓						
Medical history			✓						
Disease history			✓						
Randomization			✓						
**Interventions**									
	Acupuncture plus routine treatment			✓		✓			
	Routine treatment			✓		✓			
	Assessments			✓					
**Cognitive function assessments**									
	MMSE^a^			✓				✓	
	MoCA^b^			✓				✓	
	CDR^c^			✓				✓	
**Blood detection**									
	Serum iron metabolism indicators			✓				✓	
	SWI^d^ scanning								
	Brain iron content			✓				✓	
Safety evaluation					✓		✓		
Adverse event					✓		✓		

^a^MMSE: Mini-Mental State Examination.

^b^MoCA: Montreal Cognitive Assessment.

^c^CDR: Clinical Dementia Rating.

^d^SWI: sensitivity-weighted imaging.

### Participants and Recruitment Strategy

Participants in this study will be recruited mainly through the inpatient system of the First Affiliated Hospital of Henan University of Traditional Chinese Medicine, and we will also use the hospital’s website and WeChat public number platform for promotion and recruitment. Patients with VCI and healthy participants who are interested and whose initial screening meets our recruitment needs will be fully informed of the entire study procedure, benefits, and risks. We will conduct this recruitment with full respect for each participant’s individual wishes. We also guarantee that the right of each participant to withdraw from the study will be respected at all stages of the clinical trial.

### Inclusion and Exclusion Criteria

#### Inclusion Criteria

Inclusion criteria are as follows: (1) aged 18-75 years, male or female; (2) patient or informant reports of memory loss or other cognitive impairment lasting for at least 3 months and not using any medication to improve cognitive function prior to enrollment; (3) diagnostic criteria for VCI are met (Western medical diagnostic criteria refer to the *2019 Chinese Guidelines for the Diagnosis and Treatment of Vascular Cognitive Disorder* and Chinese medical diagnostic criteria refer to the *Diagnostic, Identification and Efficacy Determination Criteria for Vascular Dementia*); (4) imaging evidence (computed tomography or magnetic resonance imaging) to support cerebrovascular disease; (5) clear cognitive dysfunction, as assessed by the MMSE (no education: MMSE score≤17, primary school: MMSE score≤20, or junior school or above: MMSE score≤24) and MoCA (MoCA score < 26 points); and (6) consciousness and stable vital signs.

#### Exclusion Criteria

Exclusion criteria are as follows: (1) occurrence of other brain diseases that affect cognitive function, such as intracranial occupying lesions, traumatic brain injury, arteriovenous aneurysms, and intracranial infections; (2) cognitive impairment caused by hemorrhagic stroke; (3) diseases that seriously affect the cognitive examination such as abnormal visual and auditory functions, and psychiatric abnormalities; (4) history of significant cognitive decline or dementia prior to current onset; (5) other serious diseases such as immune diseases, endocrine diseases, abnormal liver, and kidney function; (6) pregnant and lactating women; and (7) coagulation disorders and treatment site infections.

### Rejection Criteria

Rejection criteria are as follows: (1) individuals who were mistakenly included without a diagnosis of VCI; (2) individuals who did not complete the treatment cycle in the enrolled study cases; (3) serious adverse events or complications that make it inappropriate to continue the experiment; (4) participants spontaneously shed, miss visits, or die during observation; and (5) receiving medications and treatments that have a significant effect on outcomes during the trial.

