### Sample Size

Previous clinical studies on patients with VCI treated with acupuncture reported that the scores on the MoCA scale of acupuncture-treated and base-treated patients with VCI at 4 weeks were mean 26.13 (SD 5.33) and mean 22.66 (SD 5.38), respectively. We set the significance level at .05 and calculated the sample size as follows:

N = 2 [(*Z*_α/2_ + *Z*_β_) σ / δ]^2^

N is the sample size in each group, and σ and δ represent the larger SD and mean difference between the 2 groups with values of 5.38 and 3.47, respectively. When α=.05 and β=.1, checking the table shows that *Z*_α/2_=1.96 and *Z*_β_=1.282. Substituting the above data into the formula, a minimum of 64 patients in the randomized acupuncture group or control group will be required, considering a 20% shedding rate.

A review of relevant studies indicates that in magnetic resonance imaging–based studies of cognitive impairment, statistical significance can be achieved with 12 or more cases [23,24]. Because of limitations in the experimental conditions (high scanning cost of magnetic resonance imaging and the need for high levels of participant cooperation during scanning), we estimate that approximately one-third of the estimated sample of patients with VCI will be included as study participants, and finally, 42 patients with VCI and 21 healthy controls will be included.

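### The rejection criteria do not separate stopping treatment from leaving the analysis; on their natural reading, acupuncture versus control becomes a completers' comparison, with bias of uncertain direction

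*Protocol article*

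**What the plan says.** The Rejection Criteria section of the protocol article follows the inclusion and exclusion criteria and is separate from both. It has five items:

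- Item (1) is about patients entered in error: "individuals who were mistakenly included without a diagnosis of VCI".
- Item (2) is about unfinished treatment, and it names "individuals who did not complete the treatment cycle in the enrolled study cases".
- Item (3) is about harm that rules out going on, put as "serious adverse events or complications that make it inappropriate to continue the experiment".
- Item (4) is about people lost from the trial, given as "participants spontaneously shed, miss visits, or die during observation".
- Item (5) is about outside therapy, described as "receiving medications and treatments that have a significant effect on outcomes during the trial".

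Under Randomization, each envelope is opened when a patient is enrolled, so an enrolled case with VCI is a randomised case. Item (1) concerns a patient's status at entry. Items (2) to (5) concern what happens after allocation.

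The Sample Size section inflates the calculated number "considering a 20% shedding rate". The Statistical Analysis section names the tests but not the set of patients they apply to. The article does not mention follow-up of rejected patients or their retention in the comparison.

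**The concern.** A patient's course after allocation can depend on the arm and on how the patient is doing. If such events decide who is analysed, the two remaining groups are no longer the groups that randomisation formed, and their difference mixes treatment effect with selection.

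The arms are not exposed to the triggers in the same way. Both have cognitive training 6 times a week for 4 weeks (24 sessions), but only the acupuncture arm also has 24 electroacupuncture sessions. The adverse reactions anticipated under Safety Evaluation and Adverse Events (pain during needling, fainting, skin injury) arise from needling. Patients and acupuncturists know the allocation. Item (5) also requires a judgement on whether another treatment affected outcomes significantly, and the article gives no criterion for it. Blinding the assessors protects the scoring of a MoCA. It does not protect the decision on whose MoCA counts.

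At stake is the only randomised comparison in the trial, with 21 patients per arm.

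**Working it through.** **Inputs.** From Sample Size: "the larger SD and mean difference between the 2 groups with values of 5.38 and 3.47, respectively", on the MoCA at 4 weeks; "When α=.05 and β=.1, checking the table shows that" the normal quantiles are 1.96 and 1.282; loss 20%; 42 patients with VCI finally included. From Randomization: 1:1, hence 21 per arm. Neither the loss in each arm nor the scores of rejected patients are given, so both are assumptions below.

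**The plan's own figure.** 2 × [(1.96 + 1.282) × 5.38 / 3.47]² = 50.5, rounded up to 51 per group. Then 51 / (1 − 0.20) = 63.75, rounded up to 64. The stated 64 is reproduced.

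**Patients lost at the plan's own rate.** 42 × 0.20 = 8.4, so about 8 patients, leaving 21 × 0.80 = 16.8, about 17 per arm. The standard error of the difference is 5.38 × √(2/21) = 1.66 with 21 per arm and 5.38 × √(2/17) = 1.85 with 17. Power for 3.47 points (normal approximation) is Φ(3.47/1.66 − 1.96) = 55% with 21 per arm and Φ(3.47/1.85 − 1.96) = 47% with 17.

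**Shift in the difference with no true effect.** If rejected patients score k SD below completers in both arms, the completers' mean in an arm that loses a fraction d exceeds that arm's full mean by d × k × 5.38. The difference between arms therefore shifts by (d_acupuncture − d_control) × k × 5.38.

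| Loss, acupuncture / control | k (SD) | Shift (MoCA points) | Size relative to 3.47 |
|---|---|---|---|
| 20% / 0% | 0.25 | +0.27 | 8% |
| 20% / 0% | 0.5 | +0.54 | 16% |
| 20% / 0% | 1 | +1.08 | 31% |
| 30% / 10% | 1 | +1.08 | 31% |
| 20% / 20% | any equal k | 0 | 0% |
| 10% / 30% | 1 | −1.08 | 31%, against acupuncture |

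**Extreme bound.** If exactly the lowest-scoring 20% of the acupuncture arm, and nobody else, is removed, the shift is 5.38 × φ(−0.842) / 0.80 = 5.38 × 0.280 / 0.80 = +1.88 points (54% of 3.47). For the lowest 10% it is 5.38 × 0.1755 / 0.90 = +1.05.

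**Between these.** Suppose 20% are lost from the acupuncture arm only, and the log-odds of loss rise by 0.5, 1 or 2 per SD of lower score. The shift is then +0.52, +0.93 or +1.41 points.

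**False-positive rate.** Simulated two-sided t-tests (20,000 runs, 21 per arm randomised, no true effect, 20% lost from acupuncture only) reject in 5.8% of runs at k = 0.5 (4.7% in favour of acupuncture) and in 9.2% at k = 1 (8.7% in favour). Without loss the rate is 5.0%.

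**The case against.** The strongest reply is that the article never says in words that rejected patients leave the analysis. Item (3) reads as a rule for stopping participation, and item (4) describes people who have already left. Data Collection and Management refers to a statistical plan that is not shown and could define the analysis set. The 20% allowance is a routine inflation for missing outcomes and does not prove removal.

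This stands as a limit on certainty: removal is a reading of the text. It remains the natural one. The list is separate from the exclusion criteria, it covers enrolled cases, item (1) is about whether a case is valid at all, and someone who has died or has already failed to complete treatment cannot be told to stop. Nor is the point about detail left to an analysis plan. An analysis of all randomised patients needs week-4 data from patients whom the protocol rejects, so the protocol wording itself must change.

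A reader might infer three stronger things that the documents do not support.

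- **That the bias will favour acupuncture.** The extra burden is real but smaller than the session count suggests. The needles are retained during the hour of cognitive training, so the documented addition is the needling and about 30 minutes of electroacupuncture, in patients described as hospitalised. Unblinded controls might also seek other treatment and trigger item (5). Differential loss is possible but not established, and its direction is open.
- **That the error is about half the planned effect.** The +1.9 requires all the loss in one arm and exactly the worst scorers removed. The 20% in Sample Size is a general rate and is not specific to an arm.
- **That harms will be under-counted.** Rejection Criteria says nothing about safety data. Table 1 schedules adverse-event collection, and the safety section plans examinations of all volunteers before and after treatment and recording of the adverse events it lists. A confirmation of the tabulation is enough.

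**Conclusion.** The concern holds in this form: the protocol lists four kinds of post-randomisation event as grounds for rejection and does not separate stopping treatment from removal from the analysis. On the natural reading, the comparison of acupuncture with control is then confined to completers.

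The size depends on assumptions that the documents cannot settle. With loss in the acupuncture arm only, the table gives a plausible range of roughly a quarter of a point to one point, against a standard error of 1.66, and the 1.88 is a bound. Non-differential loss of patients with equal prognosis causes no bias but still costs precision. The pattern 10% versus 30% reverses the sign. The point should be settled before analysis because it affects the trial's only randomised contrast and is cheap to correct.

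**What to change.** 1. State that items (2) to (5) do not remove a patient from the analysis. Leave the rules on when treatment stops as they are.
2. Seek the week-4 MoCA, MMSE, CDR, blood and SWI assessments from patients who stop treatment, where they agree.
3. Make the primary comparison all randomised patients in their assigned arm.
4. Limit item (1) to ineligibility on facts established before allocation, judged blind to arm, and report any such case.
5. Handle remaining missing outcomes by multiple imputation using baseline values and arm. This assumes that loss is at random given those variables and does not repair loss that depends on the outcome itself, so add a sensitivity analysis for not-at-random loss. Report deaths separately.
6. Keep the completers' set as a sensitivity analysis.
7. Confirm that adverse events are tabulated by arm for every randomised patient.

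The cost is revised wording in the protocol and analysis plan, a few extra week-4 assessments (about 8 patients at the plan's own 20%), and possibly a smaller effect estimate.

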### Sample Size

Previous clinical studies on patients with VCI treated with acupuncture reported that the scores on the MoCA scale of acupuncture-treated and base-treated patients with VCI at 4 weeks were mean 26.13 (SD 5.33) and mean 22.66 (SD 5.38), respectively. We set the significance level at .05 and calculated the sample size as follows:

N = 2 [(*Z*_α/2_ + *Z*_β_) σ / δ]^2^

N is the sample size in each group, and σ and δ represent the larger SD and mean difference between the 2 groups with values of 5.38 and 3.47, respectively. When α=.05 and β=.1, checking the table shows that *Z*_α/2_=1.96 and *Z*_β_=1.282. Substituting the above data into the formula, a minimum of 64 patients in the randomized acupuncture group or control group will be required, considering a 20% shedding rate.

A review of relevant studies indicates that in magnetic resonance imaging–based studies of cognitive impairment, statistical significance can be achieved with 12 or more cases [23,24]. Because of limitations in the experimental conditions (high scanning cost of magnetic resonance imaging and the need for high levels of participant cooperation during scanning), we estimate that approximately one-third of the estimated sample of patients with VCI will be included as study participants, and finally, 42 patients with VCI and 21 healthy controls will be included.

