### Conclusions

This study will provide data on the effects of Tongdu Xingshen acupuncture on cerebral iron deposition as well as somatic iron metabolism in patients with VCI. More importantly, if the hypothesis of this study is confirmed, the results would provide evidence supporting TCM acupuncture as an alternative treatment modality for VCI and lay the scientific basis for the clinical application of Tongdu Xingshen acupuncture for VCI, which may have important socioeconomic benefits.

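### The sample size is calculated as 64 per arm for 90% power, but 21 per arm are enrolled with no power stated; on the plan's own MoCA assumptions 21 per arm gives about 53%, or 45% after the planned loss.

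*Protocol article*

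**What the plan says.** The Sample Size section of the protocol article takes week-4 MoCA scores from earlier work, which "were mean 26.13 (SD 5.33) and mean 22.66 (SD 5.38), respectively" in acupuncture-treated and base-treated patients. It uses a difference of 3.47 and the larger SD, 5.38. The error rates are fixed in the same place ("When α=.05 and β=.1"), with a two-sided critical value of 1.96. The result is "a minimum of 64 patients in the randomized acupuncture group or control group will be required, considering a 20% shedding rate".

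The next paragraph departs from that figure. It states that in MRI studies of cognitive impairment "statistical significance can be achieved with 12 or more cases". It names scanning cost and the cooperation needed in the scanner as constraints, and then says "we estimate that approximately one-third of the estimated sample of patients with VCI will be included as study participants". The outcome is 42 patients with VCI, allocated 1:1 under Randomization, so 21 per arm, plus 21 healthy controls. No power, detectable difference or revised target accompanies this number.

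Elsewhere, Research Objectives lists clinical efficacy as the first of two primary objectives. The Abstract says efficacy will be examined by comparing neuropsychological scores between groups. Statistical Analysis sets P<.05 for all results.

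**The concern.** The only power parameters in the document belong to a trial about three times the size of the one being run. A reader who meets beta = .1 in Sample Size and efficacy among the primary objectives is not told what chance the enrolled trial has of detecting the MoCA difference on which the calculation was built.

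The imaging precedent does not fill this gap. That some studies reached significance with 12 or more cases says nothing about the probability that a two-arm comparison of MoCA scores will do so here. Cost and cooperation can explain why the trial is small, but they do not show what it can detect.

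What is at stake is the interpretation of the efficacy result. If the trial has roughly even odds of missing the benefit it assumes, a non-significant MoCA comparison carries little information, and the protocol should say so before the data are analysed.

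**Working it through.** **Inputs**, all from Sample Size unless noted: difference δ = 3.47; SD σ = 5.38; two-sided α = .05 (z = 1.96); β = .1 (z = 1.282); loss 20%; N defined per group; 42 patients allocated 1:1 (Randomization), so n = 21 per arm.

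**1. The plan's own figure.**
N = 2[(1.96 + 1.282) × 5.38 / 3.47]² = 2 × 5.0265² = 50.5, rounded up to 51 evaluable per arm.
51 / 0.8 = 63.75, rounded up to 64 enrolled per arm. This reproduces.
Two arms make 128; 128 / 3 = 42.7, which agrees with the 42 enrolled.
The 90% power belongs to 51 evaluable per arm; 64 is that number inflated for loss.

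**2. Evaluable size in the trial to be run.**
Full retention: 21 per arm. After the plan's 20% loss: 21 × 0.8 = 16.8, about 17 per arm. The Rejection Criteria exclude patients who do not complete treatment or miss visits, so the second figure is the relevant one if losses are as planned.

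**3. Power for 3.47 points, comparing week-4 scores without adjustment, as the plan's formula does.**
Standard error of the difference = σ√(2/n):
- n = 21: 5.38 × √(2/21) = 1.660; δ/SE = 2.090
- n = 17: 5.38 × √(2/17) = 1.845; δ/SE = 1.880

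Normal approximation, Φ(δ/SE − 1.96), and two-sample t test (noncentral t, 2n − 2 degrees of freedom):

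| Per arm | Normal formula | t test |
|---|---|---|
| 51 (plan's evaluable target) | 90% | 90% |
| 21 | 55% | 53% |
| 17 | 47% | 45% |

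**4. Difference detectable with 90% power.**
- t test: 5.5 points at 21 per arm, 6.2 at 17
- Normal formula, (1.96 + 1.282) × SE: 5.4 and 6.0

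The assumed difference is 3.47.

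**5. Expected precision.** Half-width of the 95% confidence interval = t × SE:
- n = 21: 2.021 × 1.660 = 3.36
- n = 17: 2.037 × 1.845 = 3.76

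The interval extends about as far on each side as the whole assumed effect.

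**6. Sensitivity to baseline adjustment.** The document states no adjustment and gives no baseline correlation, so the correlations below are assumptions. Adjustment reduces the SD to 5.38√(1 − ρ²). Power by the normal formula:

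| ρ | 21 per arm | 17 per arm |
|---|---|---|
| 0.5 | 67% | 58% |
| 0.7 | 83% | 75% |
| 0.8 | 94% | 88% |

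Only a correlation near 0.8 with full retention reaches the planned 90%; with the planned loss, none of these does.

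**The case against.** The strongest reply is that nothing is hidden. The protocol prints the calculated requirement, says openly that it will include about a third of it, and gives a resource reason. It never claims 90% power for 42 patients. That stands. A reader might infer that beta = .1 is asserted of the enrolled trial, but in the text it belongs to the calculation of 64. The fault is a missing statement about the size used, not a false one. Nor is there an arithmetic error, since every printed figure reproduces.

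It would also be too strong to say that the size rests on the 12-case precedent alone. The sentence that makes the reduction opens with MRI cost and cooperation. These are legitimate constraints, though they supply no power.

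A reader might take the Conclusions as promising evidence for clinical use. The words "the results would provide evidence supporting TCM acupuncture as an alternative treatment modality for VCI" follow a condition that the study hypothesis is confirmed, so this is not an unconditional promise. Likewise, the protocol does not say how a non-significant result would be read; a misreading is a risk, not a stated intention.

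Innovations and Limitations does say that the sample needs to be expanded. It connects this to the lack of double blinding and to gender imbalance, so it does not tell the reader about power.

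Finally, the power figures depend on the analysis. A separate analysis plan could specify baseline adjustment and raise them, as step 6 shows. Statistical Analysis names one-way ANOVA or Kruskal-Wallis with no covariate, and the sample size formula is unadjusted, so the unadjusted figures are the right ones to set against the plan's own calculation. They should still be labelled as such.

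**Conclusion.** The point holds as a gap between the size the protocol derives and the size it uses, in support of a primary objective. With a difference of 3.47, SD 5.38, two-sided .05 and an unadjusted week-4 comparison, the trial has about 53% power with full retention and 45% after 20% loss, against the 90% for which the calculation was made. The choice between t test and normal formula moves this by about 2 percentage points. Baseline adjustment could move it substantially, but it is not stated, and the correlation it would need is not given.

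The imaging precedent does not justify 21 per arm for the MoCA comparison. The document does not support going further, to say that the protocol misstates the power of the enrolled trial, that 42 patients is unacceptable, or that the trial has to be renamed a pilot. Calling the efficacy comparison exploratory is one option, but it is not needed to close the gap.

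**What to change.** Keep 42 patients. In Sample Size:

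- State that 64 per arm and 90% power describe the calculated requirement and do not apply to the enrolled trial.
- Give the properties of the size used, for example: with 21 per arm (17 after 20% loss) and an unadjusted comparison of week-4 MoCA scores with SD 5.38, power for a 3.47-point difference is about 53% (45%), and the difference detectable with 90% power is about 5.5 (6.2) points. If an adjusted analysis is planned, name it and the correlation assumed, and give its figures as well.
- Give the resource limit as the reason for the size. Confine the 12-case sentence to the imaging aim or remove it; it should not support the efficacy comparison.

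In Statistical Analysis, commit to reporting the between-arm MoCA difference with its 95% confidence interval (expected half-width about 3.4 to 3.8 points), and state that a non-significant result will not be taken as evidence of no effect. In Innovations and Limitations, tie the remark about a larger sample to power as well.

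The cost is wording and a less favourable stated power. No further patients, scans or changes to treatment are needed.
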